## Methods

### Study design and participants

This protocol is a randomized, parallel-group, evaluator-blind, sham-controlled clinical trial, with an allocation ratio of 1:1, prospectively registered at ClinicalTrials.gov (NCT NCT05042115) on September 4, 2021, and follows SPIRIT 2013 and TIDiER-placebo recommendations [13, 14] for clinical trials.

Individuals diagnosed with nonspecific CLBP for at least 3 months will be included, with a mean numerical pain scale (NPE) score of at least 3 points and aged between 20 and 60 years [11]. Individuals undergoing concomitant physiotherapeutic treatment, individuals with medical contraindication to exercise, smokers/alcoholics, severe vertebral or neural pathologies, previous spine surgeries, cardiorespiratory disease, CLBP as a secondary complaint, pregnancy, hearing problems, or illiteracy and those who present an increase in symptoms in the stages of the study will be excluded.

On the day of the initial assessment (M0), all eligible participants will be informed about the procedures and objectives of the study and, after agreeing, they will sign an informed consent form (ICF), being able to voluntarily interrupt their participation in the study at any experiment stage. All study procedures were approved by the Research Ethics Committee at State University of the North of Paraná - UENP (CAEE: 43063621.3.0000.8123) and followed the Declaration of Helsinki.

The procedures will be carried out in reserved rooms of the same clinic in order to avoid any type of exposure or possible embarrassment to the participants. In the event of the possibility or presence of any type of real or potential embarrassment perceived by the participants or researchers, the intervention will be stopped immediately. All procedures will be conducted by the researcher ([name]) with experience of more than 7 years in the proposed procedures, and the evaluation will be conducted by one professional of clinical physiotherapy at the State University of the North of Paraná, previously trained in outcomes measurement. To characterize the participants, the following data will be collected: gender, age, duration of pain (months), weight, height, physical activeness, and use of medication.

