### Sample size

The sample size was calculated to detect an effect between groups for the pain intensity outcome assessed using the numerical scale. For the calculation, a power of 80% and an alpha error of 5% were adopted and, based on the results obtained by Rizzo et al. [11], a standard deviation of 2.0 points and an average difference of 1.3 points were considered, which resulted in a total sample size of 52 individuals. Considering possible sample losses, there will be an increase of 15% in the sample size calculated, totalizing 60 participants. All calculations were performed on the software G*Power version 3.1.9.7 [34].

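### The sample size of 52 (60 with the allowance) does not follow from the stated inputs: a two-sample t-test needs 78 two-sided or 60 one-sided, and 60 gives about 70% two-sided power, not 80%

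*Protocol article*

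**What the plan says.** The Sample size section of the protocol article defines the target: "The sample size was calculated to detect an effect between groups for the pain intensity outcome assessed using the numerical scale". It sets the error rates ("a power of 80% and an alpha error of 5% were adopted") and the effect ("a standard deviation of 2.0 points and an average difference of 1.3 points were considered"), the latter taken from an earlier trial that it cites. It then reports the result, "which resulted in a total sample size of 52 individuals", and adds an allowance to cover losses: "there will be an increase of 15% in the sample size calculated, totalizing 60 participants". Study design and participants fixes the randomisation "with an allocation ratio of 1:1".

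The Sample size section names neither the test nor its sidedness, and gives no correlation between repeated measurements. The Outcomes section sets three moments: before treatment (M0), after the last session (M1) and four weeks later (M2). The Statistical analysis section plans a two-factor repeated-measures ANOVA and compares the groups at individual moments by unpaired t-test, or by Mann-Whitney test if the data are not normal. It analyses everyone randomised, filling gaps by last observation carried forward.

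**The concern.** A difference of 1.3 with an SD of 2.0 is a standardised difference of 0.65. For a plain two-group comparison at 80% power, 26 per arm is too few for an effect of that size. The section presents 52 as the result of its inputs, so a reader should be able to recover it from them.

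What is at stake is how the result will be read. If the trial finds no difference in pain, readers will take it as a study with 80% power to detect 1.3 points. If the real figure is nearer 62% to 70%, the chance of missing a true 1.3-point effect is about 30% to 38%, against the 20% that the paragraph implies.

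**Working it through.** **Inputs.** Difference 1.3, SD 2.0, power 80%, alpha 5% (Sample size); allocation 1:1 (Study design and participants). Sidedness is not stated, so both are shown. Standardised difference d = 1.3/2.0 = 0.65, and d² = 0.4225.

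**1. Trying to reproduce 52 as a two-group comparison.** Normal approximation, n per arm = 2(z_alpha + z_power)²/d²:
- Two-sided: 2 × (1.960 + 0.842)²/0.4225 = 37.2, so 38 per arm and 76 in total.
- One-sided: 2 × (1.645 + 0.842)²/0.4225 = 29.3, so 30 per arm and 60 in total.

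With the noncentral t distribution, 39 per arm are needed two-sided (total 78, power 80.9%) and 30 per arm one-sided (total 60, power 80.0%). Allowing for the efficiency of the Mann-Whitney test (3/pi) gives 80 and 64. None of these is 52.

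**2. Power at the planned numbers.** Two-sample t-test, noncentrality d × sqrt(n1·n2/(n1+n2)):

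| Observed (per arm) | Noncentrality | Two-sided power | One-sided power |
|---|---|---|---|
| 51 (26 + 25) | 2.32 | 62.4% | 74.0% |
| 52 (26 + 26) | 2.34 | 63.3% | 74.8% |
| 60 (30 + 30) | 2.52 | 69.7% | 80.0% |
| 62 (31 + 31) | 2.56 | 71.2% | 81.2% |

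Put the other way, 26 per arm gives 80% two-sided power for a difference of 1.58 points at SD 2.0, or for 1.3 points if the SD were 1.64.

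**3. A route that does return 52.** Take the between-group F-test of a repeated-measures ANOVA, with f = d/2 = 0.325, m moments, common correlation rho, and noncentrality f²·N·m/(1 + (m − 1)·rho). With m = 3 and rho = 0.5 (an assumption; the protocol gives no value) and N = 52, this is 0.105625 × 52 × 3/2 = 8.24, and power is 80.4%. The required N runs from 42 at rho = 0.3 to 62 at rho = 0.7.

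**4. What that route assumes.** The between-group test compares averages over all the moments. With three moments it takes the 1.3-point difference to be present at M0 as well, before any treatment. Under randomisation the expected difference at M0 is zero. With 0, 1.3 and 1.3 points:
- average difference = 2.6/3 = 0.87, and f = 0.87/(2 × 2.0) = 0.217;
- N = 52, rho = 0.5: noncentrality 3.66, power about 47%;
- N = 60, rho = 0.5: noncentrality 4.23, power about 52%.

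**5. The loss allowance.** 52 × 1.15 = 59.8, so 60 reproduces. It retains 52 up to a loss of 8/60 = 13.3%. If 15% is meant as a loss rate, 60 × 0.85 = 51, and keeping 52 takes 52/0.85 = 61.2, so 62. Between 51 and 52 observed, two-sided power changes from 62.4% to 63.3%.

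**The case against.** The strongest reply is that 78 and 60 presuppose a t-test at one moment, whereas the planned model is a repeated-measures ANOVA and a calculation from that family returns 52 exactly. It stands this far: it would be wrong to say that no method yields 52, and the three-moment calculation is a plausible origin. It does not stand as support for 80% power, because it needs an unstated correlation and a treatment difference that exists before treatment.

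Other unstated choices also come close. A two-moment version returns 52 if the correlation is 0.3, and 62 if it is 0.6. Adjusting for baseline pain would need 70, 58 or 50 for a baseline correlation of 0.3, 0.5 or 0.6. These show that the shortfall depends on the comparison used. But the protocol gives no such correlation and plans no baseline adjustment, so none of them can be credited to it.

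A one-sided test would give 80.0% with 60. The protocol does not state one-sided testing, and 60 is the number after the allowance, so this reading would leave nothing for losses.

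A reader might infer that multiplying by 1.15 instead of dividing by 0.85 is what costs the trial its power. The document does not support that. It words the 15% as an increase, not as an expected loss rate, and adding a margin in that way is common. Even if 15% were lost, the step costs one completer and under one power point. Nor is 51 the planned analysis number: everyone randomised is analysed, with the last value carried forward. Carried-forward values do not restore the missing information, but full credit for all 60 still gives only 69.7% two-sided.

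**Conclusion.** The concern holds for the base figure. The inputs printed in the Sample size section do not lead to 52 for the between-group comparison they describe: they need 78 two-sided or 60 one-sided. Two-sided power for 1.3 points is about 63% with 52, 70% with all 60 observed and 62% with 51, so the 80% claim is too high by roughly 10 to 18 percentage points.

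This rests on the protocol's own SD and difference, 1:1 allocation, an unadjusted comparison at a single post-treatment moment, and two-sided testing as the main case. A stated and justified correlation, used in an analysis that exploits it without averaging in M0, could change the figure.

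The loss allowance is a minor wording matter. Raising 60 to 62 would not bring the trial to 80%: even 62 fully observed gives 71% two-sided. The finding does not mean that the trial must enrol more people; it means that the stated power should match the stated size.

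**What to change.** Keep 60 and rewrite the paragraph:
- Name the test, the sidedness, and any correlation and number of moments behind 52.
- Replace the 80% claim with the power of 60 for a post-treatment between-group comparison of 1.3 points at SD 2.0: about 70% two-sided with no losses, and about 62% if 15% are lost and 51 are observed.
- If a repeated-measures calculation was used, say so, and say that it takes the difference to be present at M0.
- State that 60 retains 52 up to about 13% loss. If 15% is meant as a loss rate, the arithmetic is 52/0.85 = 62.

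The cost is one corrected paragraph and a less favourable power statement. No change to enrolment, outcomes or conduct is needed. For comparison, 80% two-sided power by t-test would take 78 observed, or 78/0.85 = 91.8, so 92 randomised if 15% were lost.

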### Recruitment

Participants with CLBP will be recruited from the waiting list of the clinical physiotherapy outpatient clinic at the State University of the North of Paraná, in the city of Jacarezinho, Paraná, Brazil, and through social media advertisements.

### Allocation—sequence generation

A simple randomized sequence will be created via the www.randomization.com website by a contributor external to the researchers directly involved in the research. After the initial assessment, the researcher will access the randomization envelope and carry out the intervention according to the group allocation indicated on the envelope, that is, group 1 PNE+CH+OMT or G2 PNE + CH + sham therapy.

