### Blinding

The person responsible for evaluating the outcome measures will be blinded to the allocation of intervention groups. Given the nature of the study, it is impossible to blind the researcher/therapist. At the end of the protocol, participants will be asked to report on which type of manual therapy was assigned to their treatment (sham or OMT), in order to assess blinding success [35].

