### Statistical analysis

To analyze the population profile data, we will use the descriptive statistical method and the results will be presented with mean values, medians, standard deviations, minimum and maximum values, and confidence intervals.

Data normality will be determined using the Shapiro-Wilk test, and the comparison of variables between groups at baseline will be performed using Student’s *t*-test for unpaired data for data with normal distribution or the Mann-Whitney test for non-normal data.

Comparisons of primary and secondary outcomes between groups and moments will be performed using the analysis of variance technique for repeated measures model in the two-factor scheme. Repeat measurement data will be checked for sphericity violation using Mauchly’s test, and the Greenhouse-Geisser correction will be used when sphericity is violated.

To analyze the moments, Bonferroni’s post-test for normal distribution or Dunnet’s post-test for non-normal distribution will be used, and the analysis of the different moments between the groups will be carried out using Student’s *t*-test for unpaired data with normal distribution or Mann-Whitney test for non-normal data.

The adopted statistical significance will be set at 5%. Analyses will be performed using the Statistical Package for the Social Sciences software—version 22.0 (SPSS Inc., Chicago, IL, USA) by a researcher blinded to treatments and group allocations using a coded spreadsheet. All the randomized participants will be included in the analysis, in accordance with intention-to-treat principles. To consider all participants, the missing data will be addressed according to the last observation carried forward (M0 or M1) [36]. Analysis and results from this study will be conducted by an independent biostatistician and checked for accuracy.

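### Group comparisons at M1 and M2 are not adjusted for M0 pain, and the only check on chance imbalance among 60 simply randomised participants is an uninformative baseline significance test

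*Protocol article*

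**What the plan says.** - **Allocation—sequence generation:** "A simple randomized sequence will be created via the www.randomization.com website". The list is made by someone outside the research team, and no block or stratum is named. Then: "After the initial assessment, the researcher will access the randomization envelope and carry out the intervention".
- **Study design and participants:** the trial is described "with an allocation ratio of 1:1". One researcher delivers all procedures, and entry requires a pain score of at least 3.
- **Allocation concealment mechanism and Blinding:** envelopes are opaque, sealed and numbered, and the outcome evaluator is blinded. Of the therapist the article says that "it is impossible to blind the researcher/therapist".
- **Statistical analysis, baseline:** "the comparison of variables between groups at baseline will be performed using" an unpaired t-test or, for non-normal data, a Mann-Whitney test.
- **Statistical analysis, outcomes:** a two-factor repeated-measures ANOVA is specified. The Outcomes section lists M0, M1 and M2 as the moments, so M0 is one of them. The arms are then compared at the moments with unpaired t or Mann-Whitney tests. No baseline covariate is named.
- **Sample size:** "a standard deviation of 2.0 points and an average difference of 1.3 points were considered".

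**The concern.** With about 30 people per arm, the arms can start with different average pain by chance, and baseline pain is likely to predict later pain. The plan measures M0 pain before allocation but uses it neither to balance the arms nor as a covariate.

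The baseline test does not fill that gap. Under proper randomisation its null hypothesis is true by construction, so a significant result is a chance finding. A non-significant result does not show that the arms are close enough. The two named tests also do not suit gender, which the article collects to describe participants.

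At stake is the estimate in the one trial that is run. A starting difference worth half the planned effect can shift the treatment difference noticeably, in opposite directions for the two analyses the plan names. Precision that M0 pain could supply is also lost.

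**Working it through.** **Inputs.** From Sample size: difference 1.3, SD 2.0, "a power of 80% and an alpha error of 5% were adopted", 60 people after the loss allowance. Assumed, because the article does not give them: a baseline pain SD of 1.5 to 2.0 (the entry limit of 3 truncates the scale, so it may be below the planning value) and a baseline-outcome correlation r of 0.3 to 0.7.

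**1. The plan's own figure.** The article says "which resulted in a total sample size of 52 individuals". A two-sided comparison with d = 1.3/2.0 = 0.65 needs 76 in total (normal approximation) or 78 (t-test); one-sided it needs 60. So 52 does not follow from the stated inputs. That is a separate matter. It bears on this point only because unadjusted two-sided power at 30 per arm is 0.70, which leaves little precision to spare.

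**2. Arm sizes under a simple sequence.** With Binomial(60, 0.5), exactly 30:30 occurs in 10.3% of cases, 36:24 or worse in 15.5%, and 38:22 or worse in 5.2%. Power is 0.697 at 30:30 and 0.679 at 36:24. Unequal arms are not the problem.

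**3. Chance gap in baseline pain.** The standard error is SD × √(2/30), and P(|gap| > 0.65) = 2 × [1 − Φ(0.65/SE)].

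| Baseline SD | SE | 0.65/SE | Probability |
|---|---|---|---|
| 1.5 | 0.387 | 1.68 | 9.3% |
| 2.0 | 0.516 | 1.26 | 20.8% |

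Averaging over the arm sizes of a simple sequence changes 20.8% to 21.2%. Blocking alone would therefore leave this risk practically unchanged. It comes from the small sample with no stratification on pain and no adjustment for it.

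**4. What the baseline test detects.** The threshold is t(0.975, 58) × SE. At SD 2.0 it is 2.00 × 0.516 = 1.03 points; at SD 1.5 it is 2.00 × 0.387 = 0.78 points. The test flags 5% of allocations by design. Gaps above 0.65 that go unflagged are thus about 20.8 − 5.0 = 15.8% of allocations at SD 2.0 (three quarters of such gaps) and 9.3 − 5.0 = 4.3% at SD 1.5 (just under half).

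**5. What a gap does to the result.** At SD 2.0, given a gap above 0.65 in one direction, its mean is SE × φ(1.26)/[1 − Φ(1.26)] ≈ 0.90 points. The unadjusted comparison is shifted by r × 0.90, and change from baseline by (r − 1) × 0.90. Simulation (40,000 trials, 30 per arm) agrees:

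| r | Shift, unadjusted | Shift, change from M0 | Conditional type I error, unadjusted | Conditional type I error, change |
|---|---|---|---|---|
| 0.3 | +0.27 | −0.62 | 0.07 | 0.13 |
| 0.5 | +0.44 | −0.45 | 0.11 | 0.11 |
| 0.7 | +0.63 | −0.26 | 0.17 | 0.09 |

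With M0 as a covariate the shift is about 0 and the conditional type I error about 0.05. Averaged over all allocations, every method keeps 5%.

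**6. Gain from adjustment.** At 30 per arm, power for 1.3 points rises from 0.70 to 0.74, 0.82 and 0.93 for r = 0.3, 0.5 and 0.7. A second simulation, with whole-number entry scores of at least 3, simple allocation and r = 0.5, gave 0.69 unadjusted, 0.76 with the two-level stratum 3–5 / 6–10, and 0.80 with continuous M0 pain. Given a gap of 0.65 or more, type I error fell from 0.12 to about 0.06.

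**The case against.** A reader might infer that the arms can diverge with no safeguard at all, and that the unblinded therapist's access to the envelopes undermines the allocation. The article does not support this. The sequence comes from outside the team, the envelopes are opaque, sealed and numbered, they are opened only after the initial assessment, and a separate blinded evaluator measures outcomes. A simple sequence cannot be predicted from past allocations. Who stores or logs the envelopes is detail that an article commonly condenses.

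The simple sequence is also not an error. It is valid, it meets the 1:1 ratio in expectation, and it costs under two percentage points of power at 36:24. Moving to stratified blocks now would help only later participants, since Trial status says recruitment is under way. It would also make allocations more guessable to a therapist who knows every earlier one.

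Further, M0 is a moment in the repeated-measures ANOVA, so the plan does not ignore it. Only part of a gap enters the unpaired comparisons, and the planning SD need not hold at baseline.

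All of this stands and narrows the point. It does not answer it. Concealment and blinding do not prevent chance imbalance. The group-by-moment term works on change from M0, which over-corrects whenever r is below 1. The unpaired comparisons and the baseline test are also what the article positively specifies, so this is not a detail left to another document.

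**Conclusion.** The point holds as a weakness of the analysis, not of the validity of the randomisation. A chance gap in baseline pain above half the planned effect is realistic: about 1 allocation in 11 at a baseline SD of 1.5 and 1 in 5 at 2.0. The planned baseline test misses about three quarters of these at SD 2.0 and just under half at SD 1.5. When such a gap occurs at SD 2.0, the unpaired comparisons shift by about 0.3 to 0.6 points with it, and the change-based term by a similar range against it.

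The overall 5% error rate is not threatened, and neither a failure of concealment nor a fault in the 1:1 ratio is shown. The figures rest on the assumed baseline SD, correlations of 0.3 to 0.7, and roughly normal means. The case for adjustment does not depend on the exact values: it removes the conditional shift and raises power at every correlation examined.

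**What to change.** Amend the Statistical analysis section before any unblinded analysis:

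1. Compare the arms at M1 and M2 with M0 pain as a covariate, preferably continuous and at least as the stratum 3–5 / 6–10. Do the same for every other outcome measured at baseline, using its own M0 value.
2. Remove the baseline significance tests. Show baseline by arm descriptively, with counts and percentages for categorical variables.

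The cost is a short amendment and slightly more analysis work. M0 data are already collected, allocation is untouched, and participants already randomised are covered.

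Optionally, the external contributor who prepares the envelopes could release each one against a dated log once M0 is complete. This is a minor improvement. Replacing the simple sequence by stratified blocks during recruitment is a design preference and is not requested.

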### Allocation concealment mechanism

The allocation will be concealed using opaque, sealed, numbered envelopes by a contributor external to the researchers directly involved in the research.

### Blinding

The person responsible for evaluating the outcome measures will be blinded to the allocation of intervention groups. Given the nature of the study, it is impossible to blind the researcher/therapist. At the end of the protocol, participants will be asked to report on which type of manual therapy was assigned to their treatment (sham or OMT), in order to assess blinding success [35].

### Statistical analysis

To analyze the population profile data, we will use the descriptive statistical method and the results will be presented with mean values, medians, standard deviations, minimum and maximum values, and confidence intervals.

Data normality will be determined using the Shapiro-Wilk test, and the comparison of variables between groups at baseline will be performed using Student’s *t*-test for unpaired data for data with normal distribution or the Mann-Whitney test for non-normal data.

Comparisons of primary and secondary outcomes between groups and moments will be performed using the analysis of variance technique for repeated measures model in the two-factor scheme. Repeat measurement data will be checked for sphericity violation using Mauchly’s test, and the Greenhouse-Geisser correction will be used when sphericity is violated.

To analyze the moments, Bonferroni’s post-test for normal distribution or Dunnet’s post-test for non-normal distribution will be used, and the analysis of the different moments between the groups will be carried out using Student’s *t*-test for unpaired data with normal distribution or Mann-Whitney test for non-normal data.

The adopted statistical significance will be set at 5%. Analyses will be performed using the Statistical Package for the Social Sciences software—version 22.0 (SPSS Inc., Chicago, IL, USA) by a researcher blinded to treatments and group allocations using a coded spreadsheet. All the randomized participants will be included in the analysis, in accordance with intention-to-treat principles. To consider all participants, the missing data will be addressed according to the last observation carried forward (M0 or M1) [36]. Analysis and results from this study will be conducted by an independent biostatistician and checked for accuracy.

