**Methods:**

A randomized controlled clinical trial will be conducted in participants aged 20–60 years with CLBP who will be divided into two groups. Group 1 will receive PNE and CH associated with OMT, and G2 will receive PNE, CH, and sham therapy. In both groups, 4 interventions of a maximum of 50 min and with an interval of 7 days will be performed. As primary outcomes, pain (numerical pain scale), pressure pain threshold (pressure algometer), and disability (Oswestry Disability Questionnaire) will be evaluated and, as a secondary outcome, global impression of improvement (Percent of Improvement Scale), central sensitization (Central Sensitization Questionnaire), biopsychosocial aspects (Start Beck Toll Questionnaire), and behavior of the autonomic nervous system (heart rate variability) will be assessed. Participants will be evaluated in the pre-intervention moments, immediately after the end of the protocol and 4 weeks after the procedures. Randomization will be created through a simple randomized sequence and the evaluator will be blinded to the allocation of intervention groups.

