In addition, the autonomic nervous system will be evaluated through the heart rate variability (HRV), which will be analyzed using linear methods, in the domains of time (SDNN and RMSSD) and frequency ((LF ms2, LF un, HF ms 2 , HF un and LF/HF) and by the geometric indices (SD1, SD2 and SD1/SD2) [30]. The participant will be invited to lie in the supine position on a stretcher, and the evaluator will place a heart rate monitor (Polar RS800CX) on the individual’s chest, with the objective of recording the heart rate beat by beat for 15 min, for later analysis of the HRV. After capturing the heart rate beat by beat, by the Polar RS800CX heart rate monitor (Polar Electro, Kempele, Finland), the data will be submitted to digital (Polar Pro Trainer software version 5.0) and manual filtering (Microsoft Office Excel version 15.3) to eliminate premature ectopic beats and artifacts [31], and only sets with more than 95% of sinus beats will be included in the study. From the period of greater stability of the tachogram, 1000 consecutive RR intervals will be extracted from the baseline and final moments, followed by the calculation of HRV indices using the Kubius HRV software [32]. For the spectral analysis (LF ms2, LF u.n, HF ms 2, HF u.n and LF/HF), the fast Fourier transform algorithm will be used [33].

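### Heart-rate-variability powers and ratios enter the repeated-measures ANOVA with no transformation stated, and the plan's provisions for non-normal data do not reach the group-by-moment test

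*Protocol article*

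**What the plan says.** Under Secondary outcomes, the article states that "the autonomic nervous system will be evaluated through the heart rate variability (HRV), which will be analyzed using linear methods". It lists time-domain indices (SDNN, RMSSD), LF and HF each in ms2 and in normalised units, the ratio LF/HF, and SD1, SD2 and SD1/SD2. On the spectral indices it adds: "For the spectral analysis (LF ms2, LF u.n, HF ms 2, HF u.n and LF/HF), the fast Fourier transform algorithm will be used". No logarithm or other transformation is mentioned. The abstract lists HRV among the secondary outcomes, and the Secondary objective names autonomic modulation.

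The Statistical analysis section gives one model for everything: "Comparisons of primary and secondary outcomes between groups and moments will be performed using the analysis of variance technique for repeated measures model", in a two-factor scheme. Its only attached safeguard is the Greenhouse-Geisser correction after Mauchly's test.

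Non-normality is addressed elsewhere in the same section. It says "Data normality will be determined using the Shapiro-Wilk test", and then provides:
- Mann-Whitney instead of the t-test for the baseline comparison;
- a Dunnet post-test instead of Bonferroni between moments;
- for the groups at the different moments, "Student’s *t*-test for unpaired data with normal distribution or Mann-Whitney test for non-normal data".

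**The concern.** A power in ms2 cannot be negative, and a ratio has no symmetric raw scale. Take two participants with LF/HF of 4 and 0.25. The mean of LF/HF is (4 + 0.25)/2 = 2.125, and the mean of HF/LF is also 2.125, so raw averaging says both that LF exceeds HF and that HF exceeds LF. On the log scale the two values cancel to zero whichever way the ratio is written.

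If such indices are strongly right-skewed, the largest values dominate the ANOVA error term. The Greenhouse-Geisser correction does not help, because it deals with sphericity and not with skewness. The article gives every other comparison a branch for non-normal data and leaves the one test of different change between the arms without one. At stake is whether a proportional change in autonomic indices would be detected, and whether a null HRV result reflects the treatment or the scale.

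**Working it through.** **Inputs from the article.** Sample size section: 52 participants, raised by 15%, so 52 x 1.15 = 59.8, taken as 60. With 1:1 allocation that is 30 per arm. Significance is 5%. The article states no HRV mean, SD, effect or power, so there is no HRV figure to reproduce. The 52 refers to pain (SD 2.0, difference 1.3). It reproduces as a between-groups repeated-measures ANOVA with f = 0.325, three measurements and an assumed correlation of 0.5 (power 0.804). Only the 30 per arm is used below.

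**Assumptions.** Log-normal data, log-scale SD s, within-person correlation r, and a multiplicative effect R in one arm after baseline. Outcomes are planned at M0, M1 and M2, but the HRV paragraph mentions RR series only from the baseline and final moments, so both a two-moment and a three-moment analysis were examined.

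**Two moments (M0, M1), r = 0.6.** The group-by-moment F test equals a t-test on change. On the log scale:

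- SD of change = s x sqrt(2(1 - r)); noncentrality = ln(R)/SD x sqrt(30/2); 58 degrees of freedom.
- s = 0.9, R = 1.5: SD = 0.9 x sqrt(0.8) = 0.805; ln 1.5 = 0.405; noncentrality = 0.405/0.805 x 3.873 = 1.95; power about 48%. Simulation gave 49%.

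On the raw scale, in units of the baseline mean, the effect is R - 1. With a = exp(s²) - 1 and b = exp(r s²) - 1, the variance of change is 2(a - b) in the control arm and (1 + R²)a - 2Rb in the other.

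- Same case: a = 1.248 and b = 0.626, so the variances are 1.244 and 2.178. The standard error is sqrt((1.244 + 2.178)/30) = 0.338 and z = 0.5/0.338 = 1.48.
- The normal approximation gives about 32% power. Simulation, which allows for the skewness, gave 36%.

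Simulated power over the range:

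| s | R | Raw | Log | Gap (points) |
|---|---|---|---|---|
| 0.6 | 1.5 | 79% | 83% | 4 |
| 0.9 | 1.5 | 36% | 49% | 13 |
| 1.1 | 1.5 | 21% | 35% | 14 |
| 0.9 | 1.8 | 64% | 79% | 15 |
| 1.1 | 1.8 | 41% | 63% | 22 |

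Repeat simulations agreed to within about 2 points.

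**Three moments, Greenhouse-Geisser when Mauchly's p < 0.05, 8,000 replicates.** The effect is at M1 and M2 and is set so that log-scale power is about 80%:

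| s | Raw power, r = 0.5 | Raw power, r = 0.7 |
|---|---|---|
| 0.25 | 81% | 81% |
| 0.5 | 77% | 75% |
| 0.8 | 65% | 61% |
| 1.0 | 53% | 49% |
| 1.2 | 41% | 37% |

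**Who drives the error term (r = 0.5).** The 3 most extreme of 60 participants carry 31%, 45% and 54% of the raw error sum of squares at s = 0.5, 0.8 and 1.0. On the log scale they carry 19% in each case.

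**Type I error.** In the three-moment runs, raw-scale rejection under no effect was 3% to 5%, conservative at high skew.

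**Which indices gain.** If SDNN, RMSSD, SD1 and SD2 behave as square roots of power, log SD and log effect both halve. Raw against log power is then 83% v 82% at s = 0.30, 46% v 48% at 0.45 and 31% v 35% at 0.55 (square root of a 1.5-fold effect). For roughly symmetric data such as normalised units might be (assumed mean 50, SD 15), taking logs lowers power from about 80% to 68-69%.

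**The case against.** **Silence is not a statement.** The article never says the indices are analysed untransformed, and a transformation could sit in an analysis plan that is not shown. That stands as a limit: a reader might infer that raw-scale analysis is an explicit choice, and the text does not support this. But the section does set out its handling of non-normal data comparison by comparison, and that rule omits the group-by-moment test. The point rests on this stated and incomplete rule.

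**The plan does provide for non-normality.** A reader might infer that skewness is ignored or met only in post-tests. That is wrong: Mann-Whitney is planned at baseline and for the groups at each moment. Ranks are unchanged by a logarithm, and in a randomised trial a between-arm comparison after treatment bears on the autonomic objective. In the two-moment setting its power at M1 was about 39% (s = 0.9, R = 1.5) and 51% (s = 1.1, R = 1.8), above the raw contrast but below the log contrast (49% and 63%). In the three-moment runs it was 73-75% at correlation 0.5 and 52-53% at 0.7. It softens the loss. It does not use the baseline value, does not test the interaction and gives no estimate as a ratio.

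**The skewness is assumed.** This stands. At a log-scale SD of 0.25 nothing is lost, and at 0.5 to 0.6 only about 4 to 6 points.

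**Sample size is the tighter constraint.** This is true in part. With a 1.5-fold effect and a log-scale SD of 0.9 or 1.1, the log analysis also has under 50% power. The trial is sized on pain, not on HRV.

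**Conclusion.** The point holds in a limited form. LF and HF power, LF/HF and SD1/SD2 go into the ANOVA with no transformation stated, and the group-by-moment test has no provision for skewed data. If these indices are markedly right-skewed, the cost at 30 per arm is roughly 0 to 6 points of power at a log-scale SD of 0.25 to 0.6 and about 14 to 30 points at 0.8 to 1.1. The planned Mann-Whitney tests offset part of it. The figures rest on a log-normal model, correlations of 0.5 to 0.7 and a proportional effect, none of which the article gives.

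Stronger conclusions are tempting and not supported. There is no excess of false positives. The primary outcomes are unaffected. The autonomic objective is not left without any robust test. Nothing here argues for taking logs of every HRV index. HRV is secondary and unpowered, so only sensitivity and interpretability are at stake.

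**What to change.** Add one sentence to Statistical analysis: LF ms2, HF ms2, LF/HF and SD1/SD2 are analysed as natural logarithms in the planned repeated-measures model, and between-arm effects are reported as ratios of geometric means with 95% CI. State that this scale is fixed in advance and not chosen by the Shapiro-Wilk result. Leave the normalised units untransformed, and also SDNN, RMSSD, SD1 and SD2 unless a reason is given. If an unpublished analysis plan already specifies the scale, a cross-reference is enough.

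The change needs no new data or participants. Its cost is a change in what is estimated: readers get ratios of geometric means (percentage differences) instead of mean differences in ms2. If an index proves roughly symmetric, the logarithm could cost some power, which is why the list is confined to the powers and ratios.
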